### Study design

This study is a randomized, double-blind, placebo-controlled exploratory clinical trial. After receiving written informed consent, the subjects who passed the screening criteria will be recruited and randomly divided into the intervention group or the control group at a ratio of 1:1. After 4 weeks of treatment, the patients were followed up for 12 weeks. The study flow chart is summarized in Fig. 1, and the timing of treatment and follow-up are detailed in Table 1.

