### Sample size

It is the first exploratory study to explore the efficacy of TCM in patients with AE-IPF. At present, we have not found the research data of AE-IPF treated by TCM, and the formal sample size calculation is not possible. We referred to the calculation method of the minimum sample size in exploratory clinical research, 40 participants in the intervention group, and 40 in the control group (*N* = 80 in total). The result of this study will provide data for a formal sample size calculation for further study.

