### Statistical analysis

The statistical analysis in this trial will be performed by Jiangsu Famous Medical Technology Co., Ltd. in Nanjing, China. The analysis will be based on the full analysis set, which is performed based on the ITT population.

In the descriptive data, continuous variables are described as mean (SD) and standard deviation or median and interquartile, categorical variables are described as numbers and percentages. The primary outcome of this study is treatment failure rate and all-cause mortality rate in each group. They will be compared between groups using the *χ*^2^ test or Fisher’s exact test. In secondary outcome analysis, the mMRC score for dyspnea, the SGRQ-I score for quality of life, the PaO_2_, and oxygen index will be used to analyze the difference, and differences between groups in mean change between baseline and measurements made at each time point will be analyzed by analysis of covariance. The length of hospitalization will be compared using the independent Student’s *t*-test or the Wilcoxon rank-sum test according to the normality of the data. Overall Survival, acute exacerbation rate, and intubation rate will be compared between groups using the *χ*^2^ test or Fisher’s exact test. The two groups will be compared using the 95% confidence interval method to determine superiority. SAS®, Version 9.2, performed all statistical analyses.

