There are some limitations to this study. First, there is no proven, effective treatment for AE-IPF at present. High-dose corticosteroids and antibiotics are widely used, but the dose of appropriate and duration therapy remains unclear. It will result in a very different primary treatment for each participant. Another limitation is that due to the lack of preliminary evidence-based studies, the sample size estimated by exploratory research is too small, and the follow-up time is short. The results and conclusions will be limited. However, based on the result obtained from this study, a clinical trial with a long follow-up period and a large sample size will be conducted.

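### The Statistical analysis section sets a superiority rule over two unordered primary outcomes, in a trial presented as exploratory and not sized for such a claim

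*Protocol article*

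**What the plan says.** The article's Study design section labels the trial: "This study is a randomized, double-blind, placebo-controlled exploratory clinical trial". Under Sample size it states that "the formal sample size calculation is not possible", sets "40 participants in the intervention group, and 40 in the control group", and gives the purpose: "The result of this study will provide data for a formal sample size calculation for further study". The Discussion says the trial is to assess safety and feasibility and to inform larger trials. Among the limitations it concedes that "the sample size estimated by exploratory research is too small".

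Under Statistical analysis: "The primary outcome of this study is treatment failure rate and all-cause mortality rate in each group". On the tests: "They will be compared between groups using the *χ*^2^ test or Fisher’s exact test". After the secondary analyses comes the decision sentence: "The two groups will be compared using the 95% confidence interval method to determine superiority". It names no outcome and no interval method. The section gives no alpha, no order of the two primaries, and no either/both criterion.

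**The concern.** A rule that lets an interval settle superiority is confirmatory. The rest of the article describes a trial that estimates and prepares. Followed as written, the rule permits a confirmatory conclusion from a design that was not built for one.

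Three features widen the opening:

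- There are two primary outcomes, and nothing says which one carries the conclusion.
- The sentence follows the secondary analyses without restriction, so it can be read as covering those too.
- One primary, treatment failure, partly depends on judging that symptoms or signs have not improved or that significant new ones have appeared.

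At stake is the wording of the result. A chance finding on one outcome could be reported as established superiority. A null finding could be read as no effect although its interval still includes a large benefit.

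**Working it through.** **No planning figure to reproduce.** The 80 patients come with no alpha, power, effect size or event rate.

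**Inputs**
- From the article: 40 per arm, 1:1 allocation; two primary outcomes; 95% interval; chi-square or Fisher's exact test; death within 4 weeks counts in both primaries, so the two tests are positively correlated.
- Assumed: two-sided 5% per outcome (read from the 95% interval), and event rates of 50 to 80%. The nearest figure in the article is the 55 to 80% mortality in its Background, which is in-hospital, not 16-week. It gives no treatment failure rate.

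**1. False-positive risk if either outcome is enough**

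Independent tests: 1 − 0.95² = 0.0975. In the granule's favour only: 1 − 0.975² = 0.0494.

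With correlated statistics (bivariate normal, critical value 1.96):

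| Correlation | Either direction | Granule's favour |
|---|---|---|
| 0 | 9.75% | 4.9% |
| 0.4 | 9.3% | 4.7% |
| 0.6 | 8.75% | 4.4% |
| 0.8 | 7.8% | 3.9% |

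The comparator for a single outcome is 5% and 2.5%.

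Simulation (400,000 null trials per scenario, 40 per arm, early deaths shared, seven scenarios) gave 7.7 to 11.0% in either direction with chi-square or a Wald interval, and 4.5 to 6.5% with Fisher. Values above 9.75% reflect the small-sample liberality of chi-square and Wald, not multiplicity. If both outcomes must succeed, there is no inflation.

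**2. Precision**

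Half-width = 1.96 × √(2p(1 − p)/40).
- p = 0.50: 1.96 × √0.0125 = 0.219
- p = 0.80: 1.96 × √0.008 = 0.175

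That is about 18 to 22 percentage points.

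**3. Power, two-sided 5%**

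Power = Φ{[d − 1.96√(2p̄(1 − p̄)/40)] / √(p₁(1 − p₁)/40 + p₂(1 − p₂)/40)}, where p₁ and p₂ are the control and intervention rates, p̄ is their mean and d = p₁ − p₂.

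Example, 55% v 25%: [0.300 − 1.96 × 0.1095] / 0.1043 = 0.82, so power is 79%.

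| True difference | Power at control rates of 50–80% |
|---|---|
| 10 points | 14–18% |
| 15 points | 27–32% |
| 20 points | 43–50% |
| 30 points | 78–82% |

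The difference detectable with 80% power is about 29 to 31 points.

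**4. Can the test and the interval disagree?**

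Take 22 v 13 events out of 40 and a Wald interval (assumed, as no method is named). The difference is 0.550 − 0.325 = 0.225, and SE = √(0.55 × 0.45/40 + 0.325 × 0.675/40) = 0.108. The 95% interval is 1.3 to 43.7 points and excludes zero. Fisher gives p = 0.071; chi-square gives p = 0.043. Enumerating all outcomes at true rates of 55% v 35%, Wald and Fisher disagree in about 9% of trials. The conflict is therefore mainly between Fisher and the interval.

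**The case against.** The article is a condensed document, and a statistical analysis plan may exist. An order, an alpha split, a success rule and the interval method are commonly left to that plan. The article also limits its own reach: it calls the trial exploratory, admits the size is too small and says its conclusions will be limited. A test accompanied by a 95% interval is ordinary practice.

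Most of this stands. Silence on multiplicity is not a defect by itself, and the error rates above are conditional. It does not remove the conflict, because the superiority sentence is stated affirmatively in the same article as the exploratory aim. An unseen plan could supply an order but would not reconcile those statements.

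Two stronger readings may tempt a reader, and the documents support neither:

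- **That the plan carries a 10% false-positive risk.** This assumes that either outcome suffices, counts results against the granule as well, ignores the shared deaths, and depends on the test. The article fixes no such success rule.
- **That 40 per arm cannot support a superiority claim.** Small numbers reduce power and precision. They do not by themselves raise the type I error or invalidate an interval that excludes zero, and a true difference of about 30 points would be found with about 80% power.

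**Conclusion.** The point holds as a conflict within the article. A superiority rule, not limited to one outcome and spanning two unranked primaries, stands beside a description of an exploratory trial with no sample size basis.

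Under an either-outcome reading at two-sided 5% each, a false claim for the granule has a nominal probability of about 4 to 5% instead of 2.5%; in either direction it is about 8 to 9.75% instead of 5%. Both figures depend on the inferred success rule and on the correlation, and Fisher's test lowers them. At assumed event rates of 50 to 80%, the trial was not sized to support a superiority conclusion unless the true difference is about 30 points. The risk is overclaiming; the conduct of the trial is not affected.

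**What to change.** End the decision sentence before its last three words. State that the risk difference with its 95% confidence interval will be reported for both primary outcomes as estimates for planning the next trial. No alpha split is then needed.

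If a superiority claim is kept:

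1. State one decision rule, with the test and the interval chosen to agree with each other.
2. Name the outcomes it covers.
3. Control the error across the two primaries by a fixed order, Holm's procedure or an alpha split.

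With 0.025 per outcome, the overall error is at most 5% (1 − 0.975² = 4.94% if independent). The difference detectable with 80% power then rises from about 29–31 to about 32–34 points at control rates of 50 to 80%. A fixed order leaves the first outcome at the full 5%, but the second can be claimed only if the first succeeds.

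The cost is wording only, with no extra patients or data. The downside is a more modest claim or, if superiority is kept, slightly lower power per outcome.

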## Discussion

According to the clinical manifestations and characteristics of IPF, most scholars believe that IPF belongs to lung wilt disease or lung bi in TCM [26, 27]. There are specific effects and advantages in IPF treated by TCM. Previous studies have shown that TCM is beneficial in reducing symptoms such as cough, sputum, wheezing, and dyspnea, shortening the course of the disease and improving the quality of life [16, 28], but mostly focusing on the stable period. The research on the treatment of AE-IPF with TCM is still in the exploratory stage.

Western medicine is still currently a lack of effective treatment and control measures, and the treatment of AE-IPF only includes supportive care (i.e., palliation of symptoms and supplemental oxygen) and unproven interventions (such as corticosteroids, antibiotics, or lung transplantation) [29]. According to TCM, the primary pathogenesis of AE-IPF obstructs lung collaterals and phlegm and blood stasis. IPF patients experience external pathogenic factors due to the deficiency of the lung, abnormal lung qi circulation and descending, qi stagnation and blood stasis lead to lung collateral obstruction; stagnation of qi and blood stasis affect the healthy transfusion of water, and causing turbid phlegm to accumulate in the lung. The aggravation of phlegm and blood stasis leads to the occurrence of AE-IPF. The treatment of AE-IPF should be based on reinforcing the healthy qi and eliminating the pathogenic factors. Based on nourishing the kidney and lung, and treated by resolving phlegm, activating blood, and dredging collaterals.

Based on the core pathogenesis and treatment principles of AE-IPF, we have formulated Kangxianhuanji Granule, which was widely used in clinical practice and had an excellent curative effect. However, there are still no rigorously designed clinical trials to assess the efficacy of Kangxianhuanji Granule on AE-IPF. We applied for this exploratory clinical trial to estimate the security and feasibility of the Kangxianhuanji granule for AE-IPF. The results obtained from the study will provide evidence for the future design of high-quality, large-scale randomized controlled trials.

There are some limitations to this study. First, there is no proven, effective treatment for AE-IPF at present. High-dose corticosteroids and antibiotics are widely used, but the dose of appropriate and duration therapy remains unclear. It will result in a very different primary treatment for each participant. Another limitation is that due to the lack of preliminary evidence-based studies, the sample size estimated by exploratory research is too small, and the follow-up time is short. The results and conclusions will be limited. However, based on the result obtained from this study, a clinical trial with a long follow-up period and a large sample size will be conducted.

## Trial status

The recruitment of participants is in progress. Participant recruitment began on November 19, 2019, and will be completed on December 31, 2021.

## Data Availability

The study results will be available as the published manuscripts, and no additional unpublished data are available.

## Abbreviations

AE-IPF: Acute exacerbation of idiopathic pulmonary fibrosis
HRCT: High-resolution computed tomography
mMRC: Modified British Medical Research Council
SGRQ-I: St George’s Respiratory Questionnaire for idiopathic pulmonary fibrosis
HRQL: Health-related quality of life
PaO_2_: Partial pressure of oxygen
